## Aims

2

The primary aim of the current study is to determine the feasibility of conducting a future RCT to examine the clinical efficacy and mechanisms of action of TF‐CBT and EMDR interventions purposely adapted for people with ARMS. Feasibility will be assessed through four key indicators (trial recruitment, trial retention, EMDR/TF‐CBT treatment engagement, and EMDR/TF‐CBT treatment fidelity).

The secondary aims are to (1) examine the promise of efficacy of EMDR/TF‐CBT on important clinical outcomes and the acceptability of assessment instruments to investigate the efficacy and mechanisms of action of EMDR and TF‐CBT in this participant group, (2) gather data on the safety of EMDR and TF‐CBT in people with ARMS, (3) gather qualitative data to explore the acceptability of EMDR and TF‐CBT in trial participants, and (4) gather qualitative data from trial therapists, supervisors, and other professional stakeholders to explore their views on barriers and enablers of successful implementation of EMDR and TF‐CBT in future routine mental health care for the ARMS group.

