### Design

3.1

We will conduct a feasibility randomised controlled trial (RCT) with two nested qualitative studies. The trial will be a pre‐registered (ISRCTN76699092) single‐blind parallel group RCT with three arms: EMDR+treatment as usual (TAU), TF‐CBT+TAU, or TAU alone (see CONSORT diagram provided in Appendix S1). Key feasibility outcomes will be assessed by Research Assistants (RAs) at baseline and at a 9‐month post‐randomisation assessment, with further outcomes collected at 12‐month post‐randomisation via screening of medical records.

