### Comparator: TAU

4.1

TAU will be in line with all standard and individually prescribed clinical interventions as directed by national clinical guidelines for psychosis/ARMS (National Institute for Health and Care Excellence [NICE] 2013, 2014) and the participants' clinical teams. In EDIT services and ARMS pathways within EIP services, support provided to ARMS individuals typically includes active monitoring of prodromal symptoms and the offer of preventive interventions for psychosis, in particular Cognitive Behavioural Therapy. However, TAU for ARMS individuals may differ depending on additional clinical needs and whether service users are referred to and/or managed by other primary or secondary care mental health services over the course of the RCT. In no case will the trial team interfere with teams' clinical decision making by asking to withhold referrals or interventions that would be offered to participants as part of their usual care, including other active psychological interventions. The uptake of interventions comprised in TAU will be documented via reviews of participants' medical notes for up to 12 months post‐randomisation.

### 
EMDR Intervention

4.2

Participants allocated to the EMDR+TAU arm will receive up to 24 sessions of EMDR over a 9‐month treatment window, in addition to TAU. Each session will last up to 90 min and will be audio/video‐recorded for fidelity monitoring purposes when participants consent to this. The specific protocol used as part of this trial has already been evaluated and implemented successfully in other feasibility trials conducted by the research team with clients who have already transitioned to FEP (for further details on this treatment approach, see Varese et al. 2021; Varese et al. 2024), which will be gradually refined over the course of this trial to maximize acceptability and clinical benefit for ARMS participants.

### 
TF‐CBT Intervention

4.3

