In line with recommended practice (Health Research Authority [HRA] 2023; International Council for Harmonisation [ICH] 2016), all adverse events (AEs) experienced by participants over the course of the RCT will be monitored and assessed by a clinically qualified senior researcher to establish seriousness (i.e., those resulting in death; life‐threatening circumstances; new or prolonged hospitalisations and emergency care; persistent disability or incapacity), severity, relatedness to trial procedures/interventions, and expectedness. All suspected serious SAEs will be independently assessed by the chair of an independent trial steering committee and reported to relevant regulatory bodies. To promote active monitoring of AEs, RAs will inquire about possible serious AEs during all follow‐up assessments with trial participants and via an additional phone call 4.5 months following the end of baseline assessment. Medical notes will also be monitored up to 12 months post‐randomisation to identify any unreported AEs.

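### All adverse events are to be monitored, but the only safety question put to all three arms asks about serious events, so non-serious harms are left to notes review and unsolicited reports

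*Protocol article*

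**What the plan says.** The adverse-event paragraph in section 5 (Outcomes) of the protocol article sets a wide scope: "all adverse events (AEs) experienced by participants over the course of the RCT will be monitored and assessed by a clinically qualified senior researcher". Each event is to be graded for seriousness, severity, relatedness and expectedness. Seriousness is defined there by death, threat to life, hospital or emergency care, or lasting disability.

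The same paragraph then describes how events will be found. The stated purpose is general: "To promote active monitoring of AEs". The stated method is not: "RAs will inquire about possible serious AEs during all follow‐up assessments with trial participants", and again "via an additional phone call 4.5 months following the end of baseline assessment". The remaining route is the records: "Medical notes will also be monitored up to 12 months post‐randomisation to identify any unreported AEs".

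Section 2 (Aims) makes safety a secondary aim, namely to "gather data on the safety of EMDR and TF‐CBT in people with ARMS".

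The contact schedule is in other sections. Section 3.1 (Design) gives one follow-up assessment by the research assistants (RAs): "Key feasibility outcomes will be assessed by Research Assistants (RAs) at baseline and at a 9‐month post‐randomisation assessment". Under section 4.2, participants in the EMDR arm "will receive up to 24 sessions of EMDR over a 9‐month treatment window, in addition to TAU"; section 4.3 gives the TF-CBT arm the same number of sessions over the same period. Only the therapy arms have a record form after each session (section 4.4), sessional symptom measures and an end-of-treatment tolerance questionnaire (section 5).

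**The concern.** Purpose and method do not match. The paragraph promises monitoring of all AEs and a central judgement of seriousness, but the question put to participants already selects on seriousness. An event that neither participant nor RA thinks of as possibly serious need never reach the person who is meant to grade it.

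The events most likely to be lost this way matter for trauma-focused therapy in this population: marked but short-lived distress, a temporary rise in symptoms, or self-harm that is not life-threatening and needs no emergency care. Under the article's own definition these are generally not serious.

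Two things are at stake. First, non-serious harms would be under-recorded in every arm, so the safety description carried forward to the definitive trial would be incomplete. Second, the remaining routes depend on contact with someone who notices and records, and the amount of trial contact differs by arm. If AEs are tabulated by arm, part of any difference could reflect opportunity for detection.

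**Working it through.** The plan gives no figure to reproduce. The check compares the routes of ascertainment and counts the scheduled contacts.

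**Routes by type of event (section 5)**

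| Route | Serious AEs | Non-serious AEs | Arms |
|---|---|---|---|
| RA question, 4.5-month call | asked | not asked | all |
| RA question, 9-month assessment | asked | not asked | all |
| Medical notes to 12 months | if recorded | if recorded | all |
| Unsolicited report | possible | possible | all |
| Mention in a trial therapy session | possible | possible | therapy arms only |

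**Scheduled trial contacts after baseline**
- TAU alone: 1 call + 1 assessment = 2.
- EMDR+TAU or TF-CBT+TAU: 2 + up to 24 sessions = up to 26.

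**Scheduled enquiries per participant**
- Serious AEs: 2 in every arm, so balanced by design.
- Non-serious AEs: 0 in every arm.

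**What unequal detection could do (assumed figures, none from the article)**

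Observed proportion = true proportion × probability of capture. Take a true proportion of 40% with a non-serious AE in every arm, and about 25 participants per arm (75 / 3, from section 3.2).

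- Equal capture, any value: ratio 1.0, no distortion.
- Capture 60% with therapy contact, 50% without: 0.40 × 0.60 = 24% against 0.40 × 0.50 = 20%. Ratio 1.2; 6 against 5 participants.
- Capture 80% against 40%: 0.40 × 0.80 = 32% against 0.40 × 0.40 = 16%. Ratio 2.0; 8 against 4 participants.

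The ratio equals the ratio of the capture probabilities whatever the true proportion, so the result is only as good as that assumption. The article gives no basis for choosing a value in this range.

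**The case against.** A fair defence has six parts.

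- **The text need not be exhaustive.** This is a condensed article; the question is a step to promote monitoring, and looking for unreported events implies that some are reported by other routes. Asking about possible serious events can also bring in events later graded non-serious. This stands in part: forms and scripts may well sit in the full protocol. But limiting the question to serious events is something the article states, not a detail it leaves out.
- **TAU is not contact-free.** Section 4.1 describes symptom monitoring and the offer of CBT, with no usual care withheld. This stands. A reader might infer 24 opportunities for detection against none; the count covers trial therapy sessions only, and the amount of usual-care contact is unknown. The therapy is additional to TAU, so the direction of the imbalance is plausible, but its size is not known.
- **The records are not said to differ.** A reader might infer that clinical notes are fuller in the therapy arms. The article does not say so. Session forms serve content and adherence monitoring and are not said to enter the medical notes.
- **Symptom worsening is measured.** Table 3 schedules the symptom measures, including PQ-16, CAARMS-23, PCL-5, GAD-7 and PHQ-9, at baseline and 9 months in all arms, with follow-up RAs blinded. This stands for worsening that persists to 9 months. It does not cover transient events within the treatment window, and scores are not assessed for relatedness.
- **No comparison of AEs is planned.** Section 6 specifies none, and safety is not among the four progression criteria in Table 2. This stands: distortion between arms arises only if AEs are reported by arm. Incomplete capture affects the safety aim either way.
- **A broader question may unblind.** Asking about distress could lead participants to mention therapy. This stands as a cost. Section 3.2.1 already provides for reassignment to another RA or blinded scoring of recorded interviews.

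**Conclusion.** The point holds in a limited form. The article promises monitoring of all AEs but restricts its only arm-neutral active enquiry to possible serious ones: two scheduled enquiries about serious AEs per participant, none about non-serious AEs, in every arm. Non-serious harms therefore rest on notes review and unsolicited reports. This follows from the text alone, provided the full protocol does not widen the question.

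That such events may be detected more often in the therapy arms is a reasonable inference from up to 26 against 2 scheduled trial contacts, and no more than that. A reader might go further and conclude that the therapies will look falsely harmful, or that a twofold artefact is to be expected. The documents do not support this: the capture probabilities are assumptions, usual-care contact is unquantified, and no between-arm AE analysis is specified.

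The consequence is moderate. No progression threshold is affected, but the safety information that a definitive trial would build on would be less complete, and events not asked about may not be recoverable after follow-up. The change should be made.

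**What to change.** Replace the RA enquiry at the 4.5-month call and the 9-month assessment with one scripted question about any adverse event or unwanted effect since the last contact, worded identically in the three arms. Leave the judgement of seriousness to the senior researcher, as the article already intends. Record the source of each event (RA enquiry, notes review, therapy session, other report). If AEs are reported by arm, base the main table on the routes common to all arms and show events known only through therapy sessions separately.

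No new contacts are needed. The cost is likely to be a few minutes per contact, more non-serious events to log and grade, and a small added risk of unblinding. To limit that risk, the script can ask participants not to mention their treatment; any unblinding that still occurs is handled under section 3.2.1.

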## Feasibility RCT Analysis

6

Descriptive statistics will be used to document participants' flow in the trial in accordance with all relevant fields of the CONSORT statement extension for feasibility trials (Eldridge et al. 2016). These will include: the number of referrals received per month, the source of recruitment, number of participants contacted, number of participants assessed for eligibility, number of participants consented into the trial (and reasons for non‐eligibility or withdrawal of interest, when appropriate and where given), number of participants allocated to each RCT arm (and those who did not receive the treatment allocated as intended), and the number of participants retained at the 9‐month follow‐up assessment. Furthermore, descriptive analyses of EMDR and TF‐CBT engagement data (number of sessions received by participants allocated to the EMDR+TAU and TF‐CBT + TAU arms) and fidelity data (therapy session records forms data as well as EFRS and CTS‐R data) will be conducted to estimate fidelity/adherence of the interventions received by study participants.

To examine the acceptability of assessment measures administered as part of the trial and the viability of extracting transition information and concomitant treatment data from clinical notes, all measures will be examined for completeness and reasons for missingness. There will be no formal hypothesis testing comparing the three groups for clinical effectiveness; however, summary statistics (Mean, SD, % of missing data) will be tabulated for each quantitative measure by trial arm at each time point, and unadjusted mean differences between the arms at the 9‐month follow‐up and their associated 80% CI will be calculated to provide some evidence towards the promise of efficacy of the interventions considered in this feasibility trial and inform the design of the future definitive trial (Lee et al. 2014).

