**Method:**

Seventy ARMS individuals with a history of trauma will be randomised to receive 24 sessions of EMDR plus treatment as usual (TAU), 24 sessions of TF‐CBT+TAU, or TAU alone. Feasibility will be determined against pre‐specified thresholds for recruitment, retention, treatment engagement, and fidelity. To examine the promise of efficacy of EMDR and TF‐CBT, participants will complete a battery of clinical and mechanistic measures at baseline and 9‐month post‐randomisation, including assessments of attenuated psychotic symptoms and post‐traumatic symptoms. Clinical notes will be reviewed to identify transitions to first episode psychosis up to 12 months post‐randomisation. Qualitative interviews with trial participants, therapists, and professional stakeholders will explore the acceptability of EMDR and TF‐CBT and factors to facilitate future implementation of trauma therapies in routine practice.

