### Participants

3.2

This trial will aim to recruit 75 individuals who (1) meet ARMS criteria operationalised using the updated version of the Comprehensive Assessment of At‐Risk Mental States (CAARMS‐23; Yung et al. 2023) and (2) report exposure to past traumatic events in childhood or adulthood on the Trauma and Live Events questionnaire (TALE; Carr et al. 2018). The full inclusion and exclusion criteria of the RCT are listed in Table 1.

**TABLE 1 eip70095-tbl-0001:** Inclusion and exclusion criteria.

Inclusion criteria	16 years of age or older Meeting ARMS criteria as defined by the CAARMS Capacity and willingness to provide informed consent Reported exposure to at least one potentially traumatic life events, as assessed by the TALE
Exclusion criteria	Under 16 years of age Non‐English speaking or requiring an interpreter for the intervention (the assessment battery at present can only be delivered in English) Evidence of recent or past transition from ARMS status to first episode psychosis (FEP), operationally defined as meeting CAARMS transition criteria (i.e., history of a treated or untreated psychotic episode of 1 week's duration or longer) and/or previous or current treatment with antipsychotics at dose of over 5 mg of haloperidol or equivalent for over 3 weeks Judged by the assigned care‐coordinator/responsible clinician and the research team as not sufficiently clinically stable to engage safely in a clinical trial of trauma‐focused therapy (e.g., acutely suicidal and suicide attempt in the previous 2 months; in a current mental health crisis; not in stable housing).

*Note:* ARMS = at risk mental state; CAARMS = comprehensive assessment of at risk mental states (Yung et al. 2005); TALE = Trauma and Life Events checklist (Carr et al. 2018).

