*Note:* Amber = continue but modify protocol—the future definitive trial is feasible with modifications; Green = continue to main study without modifications—feasible as it is. Red = stop—future definitive trial is not feasible. The feasibility thresholds below have been informed by and adapted from those employed in a past trial of trauma‐focused therapy for psychosis conducted by the Chief Investigator (the EASE trial; Varese et al. 2021; Varese et al. 2024), which were proposed/approved by the EASE trial TSC.

To evaluate the feasibility of completing the battery of measures to be employed in the future definitive trial, and gather outcome data to establish the ‘promise of efficacy’ of EMDR and TF‐CBT, participants will be assessed at baseline and 9‐months post randomisation follow‐up appointments using an assessment battery covering relevant clinical and mechanistic measures (see Table 3 for details). Additionally, at 12‐months post randomisation, participants' clinical notes will be screened to assess transition rates to first episode of psychosis and document the support received as part of TAU over the course of the trial. Additional data collection will be undertaken with all participants allocated to the TF‐CBT + TAU and EMDR+TAU arms of the trial over the course of treatment, and will include (1) sessional measures to monitor symptom fluctuations over the course of treatment (using the PQ‐16 and a sessional measure of post‐traumatic symptoms adapted from Peters et al. 2022); (2) measures of therapeutic alliance (by administering at session 3, session 12 and at therapy completion the Working Alliance Inventory—Short Form Revised; Hatcher and Gillaspy 2006); (3) a brief questionnaire to assess, at the end of treatment, the tolerance/acceptability of the psychological therapy they received (Devilly 2004).

**TABLE 3 eip70095-tbl-0003:** Summary of measures used to assess participant symptoms at baseline and follow‐up.

		Baseline	9‐months
Demographic information and clinical history			
Age, sex, ethnicity, employment status and occupation (if relevant), marital status, education level, disability status, self‐reported diagnosis, treatment history, duration of EDIT/Early Intervention service input if applicable, number and reasons for past psychiatric hospitalisations, current prescribed medications for mental health difficulties (including dosage), diagnosis.		X	Updated as required
At‐risk mental state related measures			

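### The 9-month between-arm differences are fixed as unadjusted although 16 measures also have a baseline score; this is valid but gives up precision by an amount that depends on an unstated correlation

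*Protocol article*

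**What the plan says.** Section 6 of the protocol article rules out testing between arms: "There will be no formal hypothesis testing comparing the three groups for clinical effectiveness". It then fixes the estimate to be reported: "unadjusted mean differences between the arms at the 9‐month follow‐up and their associated 80% CI will be calculated". The stated purpose is to give an indication of promise of efficacy and to help in designing the later definitive trial. Means, SDs and percentages of missing data are also tabulated by arm at each time point.

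Section 5 (Outcomes) says that "participants will be assessed at baseline and 9‐months post randomisation follow‐up appointments using an assessment battery covering relevant clinical and mechanistic measures". Table 3 marks 16 measures at both visits: PQ-16, CAARMS-23, CAPE-N, PCL-5, ITQ, DSPS, TMQ, PTCI-9, MCQ-PTSD, PTGI-SF, EQ-5D-5L, EPQ, GAD-7, PHQ-9, CAS-1R and the recovery questionnaire. TALE, AQ-10 and EoTT are taken at baseline only.

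Section 3.2.1 describes 1:1:1 allocation in permuted blocks of varying size and mentions no balancing on baseline severity. The sample size appears twice with different values: "Seventy ARMS individuals with a history of trauma will be randomised" in the abstract and "This trial will aim to recruit 75 individuals" in section 3.2. Both are carried through the working.

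**The concern.** The word unadjusted is a stated choice of estimator, so this is not a detail left open for an analysis plan. The trial collects and tabulates a baseline score for all 16 repeated measures and then leaves it out of the between-arm estimate.

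The arms are small. When a baseline score predicts the 9-month score, the unadjusted difference includes outcome variation that the baseline score could have explained. The practical result is a wider interval than the data allow. Seen from the arms actually drawn, two arms that start apart by chance will on average still be partly apart at 9 months for that reason alone. These are two descriptions of the same loss.

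At stake is how informative the differences are for their two stated uses, judging promise of efficacy and informing the definitive trial.

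**Working it through.** The article gives no interval width, SD or sample-size derivation, so there is no figure of its own to reproduce.

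**Inputs**
- N = 75 (section 3.2) or 70 (abstract), allocated 1:1:1 (section 3.2.1).
- Retention of 70% at 9 months. This is the lower edge of the top feasibility band in Table 2, used here as a planning value.
- Completers per arm: n = 75/3 × 0.70 = 17.5, or 70/3 × 0.70 = 16.3.
- Two-sided 80% interval (section 6), so the 0.90 quantile of t.
- Assumed: outcome SD of 1 in every arm, a linear relation between baseline and 9 months, and pairwise two-arm comparisons. The correlation r is not in the document and is varied.

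**Formulas, in SD units**
- Unadjusted half-width: t(0.90; 2n−2) × √(2/n).
- Adjusted half-width: t(0.90; 2n−3) × √[(1−r²) × (2/n) × (1 + 1/(2n−4))]. The last factor is the cost of estimating the covariate.

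**Numbers for n = 17.5**
- √(2/17.5) = 0.338.
- Unadjusted: 1.308 × 0.338 = 0.442.
- Adjusted at r = 0.5: 1.309 × √(0.75 × 0.1143 × 1.0323) = 1.309 × 0.2975 = 0.389.

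| r | Adjusted half-width, N = 75 (unadjusted 0.442) | Change in width | Adjusted half-width, N = 70 (unadjusted 0.458) |
|---|---|---|---|
| 0 | 0.449 | 1.7% wider | 0.467 |
| 0.2 | 0.440 | 0.4% narrower | 0.457 |
| 0.3 | 0.429 | 3% narrower | 0.445 |
| 0.4 | 0.412 | 7% narrower | 0.428 |
| 0.5 | 0.389 | 12% narrower | 0.404 |
| 0.7 | 0.321 | 27% narrower | 0.333 |

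The break-even is just under r = 0.2. With full retention and N = 75 (25 per arm) the unadjusted half-width is 0.368; adjusted it is 0.355, 0.322 and 0.265 at r = 0.3, 0.5 and 0.7.

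**Simulation check.** With 17 per arm and 8,000 runs for each r, the ratio of adjusted to unadjusted width was 1.017, 0.996, 0.970, 0.882 and 0.727 at r = 0, 0.2, 0.3, 0.5 and 0.7. Coverage of both intervals stayed between 79% and 81%.

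**The same loss seen conditionally.** The chance baseline difference between two arms of 17.5 has a standard error of 0.338 SD and exceeds 0.3 SD in either direction with probability 0.37. An imbalance of one standard error shifts the unadjusted 9-month difference by r × 0.338: 0.10 SD at r = 0.3, 0.17 SD at r = 0.5 and 0.24 SD at r = 0.7. This variation is already inside the unadjusted interval, so it must not be added to the widths above.

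**The case against.** The strongest reply is that nothing here is wrong. A reader might infer from the concern that the unadjusted differences are biased or their intervals invalid. They are neither: randomisation makes the difference unbiased, and the simulation shows nominal coverage. The article claims only preliminary evidence, plans no tests, and acknowledges in its Discussion that the sample size limits conclusions on effectiveness. That stands, and it limits the point to precision.

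A reader might also infer that the decision to progress is at risk. It is not: Table 2 uses recruitment, therapy engagement, retention and fidelity, and no between-arm difference. Nor are these differences the only data bearing on promise of efficacy, because transition to first-episode psychosis is collected at 12 months and symptoms are monitored by session in the therapy arms. Any baseline imbalance will be visible in the tabulated baseline means.

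A third tempting reading is that the plan is deficient because it does not mention the baseline-to-9-month correlation or the residual SD. Silence on these in a condensed article is no defect, and both can be computed later from the same data.

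The size of the gain is also open. Nine months is a long interval, and the 16 measures range from symptom scales to an economic questionnaire, so r will differ between them. At r of 0.2 or below there is essentially no gain. Nor does adjustment remove every effect of imbalance: it removes only the linear part, for that one measure.

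What remains is that the absence of testing does not excuse an avoidable loss of precision, since estimation is the whole purpose of these intervals, and the possible loss from adjusting is very small.

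**Conclusion.** The point holds as a recommendation about efficiency. The article fixes a valid but less precise estimator where 16 measures offer a better one from data already collected. At about 16 to 17.5 completers per arm, adjusting for the same measure's baseline score narrows the 80% interval by about 3% if r is 0.3, 12% if r is 0.5 and 27% if r is 0.7. It makes almost no difference near r = 0.2 and widens the interval by up to about 2% if r is near zero. The conclusion is the same for 70 or 75 randomised.

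These figures rest on the assumed r, 70% retention, equal SDs and a linear relation. The point does not extend to the progression criteria or to 12-month transition.

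**What to change.** In section 6, for each measure taken at both time points, estimate the between-arm difference at 9 months from a linear model with arm and the baseline score of the same measure, and report it with its 80% interval. Keep the raw means and SDs by arm, and show the unadjusted difference alongside if wanted.

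This changes one sentence, needs no new data and costs one degree of freedom per model. The worst case is an interval about 2% wider for a measure whose baseline does not predict its 9-month value. Reporting the baseline-to-9-month correlation and residual SD for each measure is an optional by-product that would help to size the definitive trial.
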